### Economic Evaluation

A cost-effectiveness analysis will be performed from a societal perspective. Since both effects on costs and generic health-related quality of life are to be expected, the method of economic evaluation is a cost-utility analysis. The primary effect parameter is generic health-related quality of life, measured in quality adjusted life years (QALYs). The time horizon of the study is one year, identical to the duration of the follow up in the clinical study. The immediate treatment effects (measurements at 3 and 6 months) and short-term treatment effects (measurement at 12 months) are observed in this study. It is not possible to observe long-term treatment effects (longer than12 months), since the duration of the study is limited to three years. Discounting is not relevant given the one-year time horizon. Sampling uncertainty surrounding the incremental cost-utility ratio will be estimated by non-parametric bootstrapping. Confidence intervals for the incremental cost-utility ratio will be calculated from the bootstrap results. The implications of sampling uncertainty on decision uncertainty (the probability specialised tinnitus care provided in a specialised tinnitus centre is more cost-effective than usual care) will be quantified using the cost-effectiveness acceptability curve. Sensitivity analyses will be used to show the impact of variation in non-stochastic input parameters on the incremental cost-utility ratio, such as discount rate, unit prices, and design issues. The impact of variability on the incremental cost-utility ratio arising from diversity and heterogeneity in the patient population will be examined in subgroup analyses. Costs in the analysis include direct health care costs (medical costs for prevention, diagnostics, therapy, rehabilitation and care), direct non-health care costs (travel costs) and indirect costs (productivity loss). Resource use will be measured using the case-record forms and 3 monthly retrospective cost-questionnaires. In the cost questionnaires the PRODISQ modules will be used to estimate productivity loss [27]. When available, the standard unit costs from the Dutch Manual for Cost Analysis [28] will be used. Resource use for which no standard unit costs are available will be valued using integral cost calculations. Costs from productivity loss will be quantified using the friction cost method, as recommended in the Netherlands [28].

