### Sample size calculation and feasibility of recruitment

After attending a specialised tinnitus clinic a change of 0.065 in health state utility as measured with the SF-6D has been observed [9]. To detect this difference (assuming a two-sided significance level = 0.05, power = 80%, standard deviation of the difference = 0.15), 86 persons per group are needed. Taking into account 15% loss to follow up, the required sample size is 99 persons per group (198 persons in total).

Approximately 400 individuals suffering from tinnitus apply to TCL yearly. We expect this number to stay stable or even increase in the coming years. Therefore it is expected that it will not be necessary to actively recruit patients for this trial.

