### Patient allocation and randomization

Research information in written format and a declaration of willingness to participate in the trial will be sent to all new patients of the Tinnitus Centre Limburg that are registered with subjective tinnitus complaints. If a patient declares that he or she is willing to participate in the study they will be invited for the baseline measurement. This face-to-face contact will be used to determine whether the patients understood the information correctly and a written informed consent will be obtained. If they agree, a hearing test will be performed to determine the level of hearing loss and the patients are asked to fill in the tinnitus questionnaire (TQ) [15] to determine the severity of the tinnitus. Based on the Fletcher Index and the scores on the TQ the patient will be randomly assigned to one of the treatment groups. Since treatment depends on tinnitus severity and the severity of hearing loss it will be important that these two prognostic factors are equally presented in the UC group and the TCL group.

Treatment allocation will be achieved by block randomisation (four blocks; A, B, C & D) to ensure equal and balanced groups. A randomization list was generated using randomization software. An equal number of patients will be allocated to the TCL group and the UC group. Patients with a score equal to or less than 46 on the TQ and a Fletcher Index below 60 dB will be allocated to block A. Patients with a score equal too or less than 46 on the TQ and a Fletcher Index equal to or above 60 dB will be allocated to block B. Patients with a score above 46 on the TQ and a Fletcher Index below 60 dB will be allocated to block C. Finally, patients with a score equal to or below 46 on the TQ and a Fletcher Index above or equal to 60 dB will be allocated to block D. The randomization procedure will be performed by an independent person at a location outside TCL.

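### The interval planned for the cost-utility ratio has no condition for a QALY difference near zero, and could not be read in about one trial in five at the planning values

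*Protocol article*

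**What the plan says.** Research question 4 in the protocol's Objective section asks about cost-effectiveness. The Economic Evaluation section answers it with a cost-utility analysis over one year, with QALYs as the effect. On precision it says "Sampling uncertainty surrounding the incremental cost-utility ratio will be estimated by non-parametric bootstrapping", and then "Confidence intervals for the incremental cost-utility ratio will be calculated from the bootstrap results". It does not name the type of bootstrap interval. It sets no condition for replicates in which the QALY difference is zero or negative, and it mentions neither net monetary benefit nor separate intervals for the cost and QALY differences. It does plan an acceptability curve for decision uncertainty, and it examines the ratio in subgroups.

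The planning values are in the sample size section. The effect comes from an earlier clinic study, in which "a change of 0.065 in health state utility as measured with the SF-6D has been observed". The calculation is made "assuming a two-sided significance level = 0.05, power = 80%, standard deviation of the difference = 0.15", and concludes that "86 persons per group are needed".

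**The concern.** The ratio is the cost difference divided by the QALY difference. It runs off to plus or minus infinity as the denominator nears zero, and its sign alone does not say what it means. A negative ratio can be cheaper and better, or dearer and worse. A positive ratio can be dearer and better, or cheaper and worse. When replicates fall on both sides of a zero QALY difference, ordering them by ratio mixes results with opposite meanings.

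A finite interval can still be computed and printed, so the reader would not see the failure. A negative lower limit could be read as possible savings when it comes from replicates in which the specialised care costs more and does less. The interval printed beside the main economic estimate would then mislead.

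**Working it through.** **When the interval fails.** Write dC and dE for the estimated cost and QALY differences, sC and sE for their standard errors, and sCE for their covariance. Under a normal approximation, the 95% confidence set for the ratio R (Fieller's method) is all R with

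(dC − R·dE)² ≤ 1.96² × (sC² − 2R·sCE + R²·sE²).

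Collected on one side, the coefficient of R² is dE² − 1.96²·sE². If it is positive, the set is an ordinary interval. If it is negative, the set is two separate rays or the whole line. It is negative exactly when the 95% interval for the QALY difference includes zero. The question is therefore how often that happens.

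**Inputs.** Effect 0.065, SD 0.15, two-sided 5% level, 80% power and 86 per group come from the sample size section. Equal allocation comes from the randomization section. Visits at 0, 3, 8 and 12 months come from the Data collection section. The documents give no SD for QALYs and no cost figures.

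**The plan's own figure.** n = 2 × (1.960 + 0.842)² × 0.15² / 0.065² = 83.6, so 84 per group, or 85 with the t distribution. The stated 86 is within two patients. Power at 86 is 81%.

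**Planning values taken as the QALY difference.**
- SE = 0.15 × √(2/86) = 0.0229
- Expected z = 0.065 / 0.0229 = 2.84
- P(95% interval includes zero) = Φ(1.96 − 2.84) = 0.19

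**Gain accruing over the year.** QALYs are the area under the utility difference, which starts at zero at baseline:
- Full effect at month 3 and kept: 0.065 × (0.25/2 + 0.75) = 0.0569
- Reached at month 8: 0.065 × (0.667/2 + 0.333) = 0.0433
- Linear to month 12: 0.065 / 2 = 0.0325

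The Economic Evaluation section refers to a 6-month rather than an 8-month measurement. That does not alter the month-3 case.

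Chance that the 95% interval for the QALY difference includes zero, 86 per group (SDs of 0.10 and 0.20 are assumed):

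| Expected QALY gain | SD 0.10 | SD 0.15 | SD 0.20 |
|---|---|---|---|
| 0.065 | 1% | 19% | 43% |
| 0.0569 | 4% | 30% | 54% |
| 0.0433 | 19% | 53% | 71% |
| 0.0325 | 43% | 70% | 81% |

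If the SD shrinks in proportion to the gain, the figure stays at 19%.

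**Behaviour of a percentile interval.** A simulation used 2,000 trials with 1,000 normal-approximation replicates each, uncorrelated costs and effects, and assumed cost differences of 500 to 2,000 with SDs of 3,000 to 5,000. Percentile intervals for the ratio covered the truth in about 95% to 98% of trials overall. Where the QALY interval excluded zero, coverage was about 95% to 97% for gains of 0.057 to 0.065, and 90% to 96% for 0.0325. Where it included zero, coverage was mostly 99% to 100%. High coverage does not help there, because the limits no longer separate dominance from being dominated. Fieller's set covered about 94% to 96% throughout.

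**The case against.** A reader might infer that the plan orders raw ratios and takes percentiles, that the problem arises often at the trial's own effect and size, and that the interval therefore has no meaning. The documents do not support that.

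- **Method.** The text says only that the interval comes from the bootstrap. A Fieller-type interval or an ordering that respects quadrants would also fit, and a condensed article may leave that choice to a fuller document. This stands against any charge of a wrong percentile method. It does not remove the point: the commitment to an interval is unconditional, and no finite interval of any type can represent an unbounded or split set.
- **Frequency.** On the stated figures the problem arises in about one trial in five. With 0.065 as the QALY gain, a trial that observes exactly that value has only 0.2% of replicates at or below zero. Higher rates need an accrual pattern and a QALY SD that the protocol does not give. The SD could also be smaller. If 0.15 is the SD of change at each visit, the area-under-the-curve weights shrink it too, to at most 0.15 × 0.875 = 0.131. With 84 per group and a gain of 0.0569, the chance is then 20% if visits are perfectly correlated, 12% at correlation 0.7 and 7.5% at 0.5 (assumed correlations). This stands, and is why a range is given.
- **False savings.** How often a misleading negative lower limit would appear depends on costs, which the documents do not give. No rate is claimed here.
- **Acceptability curve.** Built from the joint replicates, it stays valid when the QALY difference changes sign, so the adoption decision need not rest on the ratio interval. This stands and limits the consequence, but the plan still promises to report the interval.

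**Conclusion.** The concern holds in conditional form. The plan promises an interval for the ratio whatever the QALY difference turns out to be. That interval cannot be interpreted in trials whose 95% interval for the QALY difference includes zero, and it is usable in the rest.

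The chance of the bad case is about 19% at the planning values. It is about 30% if the full effect arrives at month 3 with a QALY SD of 0.15, and 4% to 54% at that gain for SDs of 0.10 to 0.20. These figures treat an SF-6D change and its SD as if they described the between-group QALY difference on the HUI3, use a normal approximation and assume 86 analysed per group. If ratio intervals were also reported for subgroups, which the text does not say, a subgroup of half the size (43 per group, assumed) would face 48% at 0.065 and SD 0.15.

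The weakness lies in how the main economic result is reported. The acceptability curve and the clinical analysis are unaffected.

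**What to change.** Replace the sentence on confidence intervals with wording such as: *Uncertainty will be reported as bootstrap 95% confidence intervals for the cost difference, the QALY difference and the incremental net monetary benefit at stated willingness-to-pay values, with the cost-effectiveness plane and the acceptability curve. The ratio will be given as a point estimate, with a confidence interval only if practically all replicates lie in one quadrant.* The share that counts as practically all should be set beforehand.

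Net monetary benefit is the willingness-to-pay value times the QALY difference, minus the cost difference. It has no denominator, so its interval behaves whichever side of zero the QALY difference falls.

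The cost is one sentence; the same replicates serve and no new data are needed. The downside is that the ratio may be reported without its own interval. The one-quadrant rule is also somewhat strict: it withholds the interval when only the cost difference straddles zero, although the ratio can still be ordered then.

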### Ethical considerations

Patients will be informed verbally and in written format about the research project before they sign the informed consent form. Participants can retreat from the study at any moment. This will have no influence on their further treatment.

The study protocol has been reviewed and approved by the Medical Ethical Board of the Rehabilitation Foundation Limburg.

The scientific merits of the study protocol have been reviewed in the consecutive phases of research funding process by the independent reviewers of the funding organization ZonMw, the Netherlands Organization for Health Research and Development.

## Discussion

### Potential strengths of the study protocol

#### Design

To our knowledge this is the first randomized controlled clinical trial that evaluates a comprehensive multidisciplinary treatment of tinnitus versus care as usual. A particular strength is the randomization procedure, in which allocation is concealed. Randomization is done at the patient level and stratified on degree of hearing impairment and tinnitus severity. This procedure is performed by an external independent person.

#### Sample size

To our knowledge this is the first study evaluating a comprehensive multidisciplinary treatment of tinnitus that includes a large sample size. At least 198 patients with tinnitus will be included in the study. As a result most statistical procedures will be robust against violations of assumptions that have to do with normality.

#### Recruitment strategy

In this randomized controlled trial every recruited patient experiences tinnitus to be one in three of their major complaints. Since tinnitus does not have to be the primary problem it is ascertained that different severity levels of tinnitus will be evaluated in this study.

#### Competence of health care professionals

Every discipline is trained to perform the intervention in a uniform way. To get insight into their actual performance, every professional is required to register all activities during all treatment-related activities during patient visits. This registration will be used to search for factors related to the intervention that might influence effectiveness.

### Potential limitations of the study protocol

#### Intervention

There is no uniform way of treating tinnitus in the audiological centres in the Netherlands. In order to model usual care treatment, a telephone survey was conducted amongst all audiological centres. This implicates that the currently implemented form of usual care is standardized, whereas in real practice clinical variation in treatment is expected.

#### Randomization approach

Randomization on patient level could lead to contamination, and bias the results of this study. However, the influence of contamination is minimised since patients in the usual care group have no access to the intervention offered by TCL-specialists and vice versa. Nevertheless it is possible that specialists that provide the usual care treatment, are more attentive to the usual care group than would be expected if treatment was provided in an independent centre. As a result our findings may be conservative.

## Conclusion

This study will provide information on whether a comprehensive, multidisciplinary treatment is more effective and efficient care for tinnitus patients. The results will also show whether the specialised treatment improves quality of life and patient satisfaction. If the intervention is proven to be effective, implementation of the intervention is considered and anticipated. First results are not expected before the beginning of 2010.
